#### Primary infant outcomes

Preterm birth (> 20 weeks gestation or 400 g [Australian definition of viability] and < 37 weeks’ gestation)Healthy baby (live born, singleton, > = 37 weeks gestation, 2500–4499 g birthweight, Apgar score at 5 minutes ≥7)Exclusive breast feeding at discharge

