Workforce strategy	No specific pathways to support First Nations MIH workforce.	Supportive career pathways with First Nations MIH workers embedded in the team with cadetships (or similar) to support midwifery education for First Nations persons. Aboriginal Family Support Workers (or similar) work side-by-side with midwives.
Continuity	No continuity of midwifery carer through antenatal, intrapartum and postnatal continuum. Care is fragmented and women see multiple providers.	Continuity of midwifery carer networked from community to a higher-level service, offering 24/7 care from a named midwife from first presentation in pregnancy until handover to child health services 6 weeks after birth. Midwifery Group Practice (caseload) midwife providing clinical care in collaboration with the extended workforce based on need (e.g. psychologist, social worker, obstetrician, paediatricians, sexual and reproductive health).
Strengthening family capacity	No maternity programs focussed on strengthening family capacity and/or cultural connection in relation to services offered through this hospital. Women may enrol in external programs.	Programs that focus on strengthening family capacity and cultural connection in relation to MIH, integrated with the BoC service.
Place of birth	No out-of-hospital option. Hospitals do not recognise or incorporate the knowledge, values and birth aspirations of First Nations people.	During the first and second phase of the new care model, all intrapartum care will occur in hospitals. If feasible, a free-standing, community-based birth centre will be set up and available for First Nations women with uncomplicated pregnancies (Category A according to consultation and referral guidelines) [18]; women with complex pregnancies (Category B or C) will birth in the local or tertiary hospital. Birth care will incorporate traditional practice; recognise the connection with Land and Country; incorporate holistic health; value both First Nations and non-First Nations ways of knowing, learning and risk assessment; and will provide a culturally competent service.

Note: *MIH* Maternal and Infant Health

^a^Some sections reproduced from Kildea, Gao et al. [19] Permission not required under licence CC BY-NC-ND 4.0

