### Study components

Using quantitative and qualitative research methods; including clinical and cost-effectiveness data, surveys including questionnaires with validated tools and open response items, interviews, yarning circles and field notes, we will ascertain:Maternal and infant health outcomes (effectiveness): for women obtaining maternity care through *Minga Gudjaga* (Mother & Baby) at Waminda or through BiOC North at IUIH. Routinely collected mother and baby clinical outcomes will enable service effectiveness analysis from commencement of the new service compared with baseline data (standard care) for both sites.Service acceptability: maternal surveys will be undertaken at three time points; approximately 36 weeks antenatally, 2 and 6 months postnatally (see Table 2 & Additional File 2 indicating scales and tools used). A qualitative research component will explore pregnancy, birthing, postnatal and early parenting experiences of a subset of women and will explore cultural safety.Services feasibility, cost-effectiveness and sustainability: Staff and key stakeholder perspectives and experiences will be gathered and will incorporate workforce issues when analysing feasibility and sustainability. A cost-effectiveness analysis of care from the first antenatal visit until 6 weeks after birth will be undertaken by extracting and comparing data on service items, health conditions and diagnoses (therefore procedures and treatments).

**Table 2 Tab2:** Summary of secondary outcome measures, data collection time points and tools

*#*	*Outcome*	*Method of data collection*	*36 weeks*	*At birth*	*2 months*	*Between 2 & 6 months*	*6 months*
*Cultural safety outcomes*							
1	**Women’s cultural safety views and experiences**	SUR QUAL			X	X	
2	**Women’s experiences of (dis)respect**	SUR QUAL			X	X	
3	**Women’s experiences of discrimination/racism**	SUR QUAL	X		X	X	
*Maternal outcomes during pregnancy, birth and the postnatal period*							
4	**Women’s feelings of control during labour and birth** (rated on a 0–10 scale)	SUR QUAL			X	X	
5	**Smoking status at first antenatal visit** (yes/no)	SUR MEDREC	X (At first AN visit, < 20 weeks, 20 + 1 wks - birth)	X	X		
6	**Experienced continuity of care** measured with 3 subscale scores of the Nijmegen Continuity Questionnaire (NCQ) pregnancy adaptation	SUR QUAL			X	X	
7	**Pharmacological analgesia in labour** (regional [epidural/spinal] and/or narcotic analgesia, nitrous oxide gas)	MEDREC		X			

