### Study participants & eligibility

#### Inclusion/exclusion criteria

##### Cohort study

Routinely collected data will be extracted for all women within the historical and intervention time periods who gave birth (or were booked to give birth) to a First Nations baby in the study sites (2013–2022). Exclusions will be based on standard and/or previously used methods to ensure validity and rigour.

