#### Power and sample sizes

BOOSt has been powered to detect a clinically significant change in preterm birth [53]. Preterm birth rates for First Nations babies in the Illawarra Shoalhaven Local Health District have been reported over a recent 5 year period as between 10.3 and 17.5%, average 12.9%. Based on our observations in the IBUS study [19], we propose a minimum treatment effect of 50% reduction (Odds ratio OR 0.5) for the preterm birth rate in the innovation arm. During recruitment, we will aim to access routinely collected maternity data for approximately 687 women at the rural site and 614 from the urban site (based on an estimated 20% attrition rate). From commencement of the new model of care, we will aim to obtain data from a minimum of 296 births (rural site) and 264 (urban). Given small numbers in the rural site (~ 120 births of First Nations babies attending Birthing on Country per year) and a ~ 3.5 year post-intervention study timeframe, we estimate 70% of the total sample to be in the pre-intervention group and 30% post-intervention. To detect this difference with 80% power and a type 1 error of 5%, and factoring exclusions for ~ 7% twin babies/babies with fetal anomaly, and 10% missing data, 983 women/births in total are needed, which includes 687 in pre-intervention and 296 in post-intervention groups. This sample size will also enable enough power for primary infant and maternal outcomes. For the urban site, the required sample size would be 878: 614 in pre-intervention and 264 in post-intervention groups. For the sub-studies, the sample size will be determined according to qualitative research conventions and considerations around data saturation.

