#### Quantitative data

##### Health services and other routinely collected data

Anonymous data from all women attending the site hospitals and health services during the study period will be extracted and analysed by birth model of care. Quantitative analyses will compare maternal and infant health outcomes between the baseline cohort (both sites) and Birthing on Country service innovation cohort (both sites), as well as standard care/concurrent and historical control groups, and non-First Nations groups (where available).

The clinical and costing outcomes data will be derived from routinely collected electronic healthcare databases at each site. Data will be imported to Stata® or Statistical Package for Social Sciences (SPSS®). While data will initially be re-identifiable (with unique study number) all patient identifiers will be removed. Data cleaning and coding decisions will be documented.

Analysis will be performed with the latest version of the appropriate software and statistical significance will be determined at the 0.05 level. Binary outcome measures will be presented using odds ratios with 95% confidence intervals. Several methods will be used to address selection bias e.g. multivariate logistic regression models, linear regression models, propensity score matching (identifies and controls for confounders e.g. the presence of pregnancy complications), and multilevel modelling controlling for clustering factors. Longitudinal outcomes will be analysed with generalized estimating equations to account for the correlation between observations repeated in the same person. We will use trend analysis to compare rates of preterm birth between First Nations and non-First Nations women, which will demonstrate if this inequity has reduced.

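### Preterm births that occur before a woman joins the service cannot count in the innovation group, so the planned yes/no comparison leans modestly toward the service

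*Protocol article*

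**What the plan says.** Under Primary infant outcomes the outcome is "Preterm birth (> 20 weeks gestation or 400 g [Australian definition of viability", with births before 37 weeks counted, one definition for all groups.

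Under Cohort study (inclusion/exclusion criteria) routine data are extracted, for both periods, for women "who gave birth (or were booked to give birth) to a First Nations baby in the study sites (2013–2022". Exclusions are left to standard or previously used methods, and no rule about gestation at entry is given.

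The innovation group is described by attendance. Study components sets out effectiveness "for women obtaining maternity care through *Minga Gudjaga* (Mother & Baby) at Waminda or through BiOC North at IUIH". Power and sample sizes assumes about 120 "births of First Nations babies attending Birthing on Country per year" at the rural site. Health services and other routinely collected data says that records "will be extracted and analysed by birth model of care", against baseline, historical and concurrent standard-care groups.

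Table 1 (Continuity) describes the service as "offering 24/7 care from a named midwife from first presentation in pregnancy until handover to child health services 6 weeks after birth", with no latest gestation for joining. The same Health services section gives odds ratios for binary outcomes and lists, as examples, logistic and linear regression, propensity score matching and multilevel models against selection bias.

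**The concern.** An innovation woman is, by construction, still pregnant on the day she joins. If she joins after 20 weeks, the time from 20 weeks to joining is event-free for her and belongs to the counted window. A historical control needs to survive no such interval: a birth at 27 weeks counts whether or not she had yet been seen. This is left truncation, and it can only lower the innovation group's preterm rate.

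Against concurrent standard care the distortion is about twice as large, because the woman who gives birth before joining is missing from one group and added to the other. Normal birth and healthy baby both require at least 37 weeks, so they inherit the same tilt. Late first visits are expected: a first visit before 14 weeks is itself a primary outcome.

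**Working it through.** **1. The plan's own figure.** Inputs from Power and sample sizes: 12.9% preterm, a halving to 6.45%, 80% power, 5% type 1 error (taken as two-sided), 70:30 split, 7% exclusions and 10% missing data. The pooled two-proportion formula gives about 571 controls and 816 women in total. 816 / 0.83 = 983, the stated rural total. The sizing therefore treats preterm birth as a yes/no outcome in two complete groups, with no allowance for entry time.

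**2. Is the innovation group a subset?** About 120 attending births a year are assumed at the rural site. The article reports more than 453 First Nations births in 2018 in the Illawarra Shoalhaven area. The areas may not coincide, but the contrast fits grouping by attendance rather than by period.

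**3. Bias under no effect.** Let p be the preterm risk in all women, and m the share of would-be innovation preterm births that precede joining.

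- Innovation odds: p(1 − m)/(1 − p)
- Historical odds: p/(1 − p), so the odds ratio is **1 − m**
- Concurrent group of equal size that receives the missed births, odds p(1 + m)/(1 − p), so the odds ratio is **(1 − m)/(1 + m)**

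**4. Size of m.** The documents give neither entry gestations nor the spread of preterm births, so all of this step is assumption: 8% of preterm births at 20–27 weeks, 11% at 28–31 and 81% at 32–36. Women joining evenly over 20–27 weeks have on average 4% of preterm births behind them. For women joining evenly between 28 and 34 weeks, the cumulative share is 0.08 at 28, 0.19 at 32 and 0.19 + 0.81 × 2/5 = 0.514 at 34, so the mean is (4 × 0.135 + 2 × 0.352)/6 = 0.207. A somewhat later spread, with a mean near 0.25 to 0.26, gives innovation rates of 12.67%, 12.54% and 12.37% in the three scenarios.

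| Join after 28 wk / at 20–27 wk | m, spread to 34 wk | OR historical | OR concurrent | m, later spread | OR historical | OR concurrent |
|---|---|---|---|---|---|---|
| 6% / 12% | 0.06 × 0.207 + 0.12 × 0.04 = 1.7% | 0.98 | 0.97 | 2.0% | 0.98 | 0.96 |
| 10% / 16% | 0.10 × 0.207 + 0.16 × 0.04 = 2.7% | 0.97 | 0.95 | 3.2% | 0.97 | 0.94 |
| 15% / 20% | 0.15 × 0.207 + 0.20 × 0.04 = 3.9% | 0.96 | 0.92 | 4.7% | 0.95 | 0.91 |

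A separate null simulation, with 50 to 65% of preterm births at 34–36 weeks, gave historical odds ratios of 0.94–0.96 if 30% join after 20 weeks and 0.89–0.92 if 50% do. With all entry by 20 weeks it gave 1.00.

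**5. Scale against the noise.** After losses of 1 − 0.93 × 0.90 = 16.3%, the rural groups are 687 × 0.837 = 575 and 296 × 0.837 = 248. The standard error of the log odds ratio is about 0.23. The later-spread rates fall short of 12.9% by 0.0023 to 0.0053, which is 0.6 to 1.3 births among 248 and 0.09 to 0.21 standard errors. In the simulation, two-sided type 1 error was 5.4–5.7% at 30% late entry and 6.4–8.0% at 50%.

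**6. Could it produce 0.5?** Against historical controls 1 − m = 0.5 needs m = 50%. Against the equal-sized concurrent group (1 − m)/(1 + m) = 0.5 needs m = 33%. The scenarios above reach at most 4.7%.

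**The case against.** The strongest reply is that ordinary adjustment can remove this. Among women whose first visit is at week w, both groups were pregnant at w and share the null risk (p − c)/(1 − c), where c is the preterm risk before w. Stratifying or matching on first-visit week therefore restores an odds ratio of 1.00, and a simulation under the assumptions above confirmed it. The listed methods are examples, and no covariate set is fixed. A reader might infer that no regression or matching could cure the bias. The documents do not support that: the bias arises when entry gestation is ignored. What stands is that the article nowhere names entry gestation, and that first-visit timing does not suffice for women who transfer in after starting standard care.

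Second, the unspecified exclusions could contain an entry rule, and extraction covers booked women in both periods. Assignment by booking is therefore not ruled out, and a comparison of all women by period would not have this bias. That tempers confidence. But the booking phrase defines whose records are extracted, while the grouping statements point to attendance.

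Third, a reader might add controls with no antenatal care and reach odds ratios near 0.88. That figure rests on assumed numbers and preterm rates for such women, counts some early births twice, and is otherwise confounding by non-attendance. It is not used here.

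**Conclusion.** The mechanism and direction hold on the article's own definitions: a 20-week outcome window, controls not conditioned on reaching a service, innovation women grouped by attendance, and no upper gestation for joining. The size is modest: an odds ratio under no effect of about 0.95 to 0.98 against historical controls and about 0.91 to 0.97 against an equal-sized concurrent group. It matters most for the concurrent comparison. These figures rest wholly on assumed entry gestations and an assumed gestational spread of preterm births, and heavier late entry would enlarge them. A reader might infer that the service could appear to halve preterm birth with no effect; the arithmetic excludes that in any plausible range. The point is worth acting on because the bias always runs one way, acts on the powered outcome, does not shrink with more women, and is cheap to remove.

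**What to change.** In Health services and other routinely collected data, state that preterm birth is analysed with delayed entry on the gestational-age scale. Pooled weekly logistic regression is one suitable form and keeps an odds ratio, though a weekly one. Each woman is at risk from the later of 20 weeks and her first visit in her model of care, until birth or 37 weeks. A woman who transfers into the service counts under standard care until she joins. Report the planned all-women odds ratio alongside, since the sizing rests on it.

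Use restriction to women in care by 20 weeks only as a sensitivity analysis: early attendance is something the service aims to change and is itself a primary outcome.

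The cost is mainly analysis wording, since first-visit timing is already needed for a primary outcome. Women with no antenatal visit leave the delayed-entry analysis, some person-weeks are lost, and the date of joining the service must be obtained for transfers.

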#### Secondary outcomes

Secondary outcomes will be assessed in these key areas:Other maternal and infant health and wellbeing status indicators, behaviours and outcomesServices acceptability, effectiveness and cost-effectivenessServices feasibility and sustainability (e.g. number of functioning services, funding attained, indicators of service use, transfers etc).

A full list of secondary outcomes and data sources is summarised in Table 2.

#### Integrated Process Evaluation & Process Outcomes

BOOSt incorporates a comprehensive evaluation protocol to enable monitoring and reporting on what works, for whom, how and why, and in what circumstances. The evaluation will include: a process evaluation to articulate development and implementation, describe contextual factors and mechanisms in operationalising the new Birthing on Country care models; as well as the analysis of feasibility and service sustainability. We consider the following to be critical elements of the innovation and they will be explored in the evaluation: enactment of First Nations governance and the mechanisms supporting it, workforce development; cultural strengthening; family-centred service orientation; and the implementation of the maternity service redesign.

Process outcomes: the components of routine maternity care alongside the proposed key ingredients of a Birthing on Country service are described (Table 1). Related components will be analysed during implementation, including workforce pathways, numbers and types of staff needed and recruited, First Nations recruitment, staff retention, caseload numbers for midwives, health care team cohesion and collaboration etc. First Nations governance indicators will include the functioning of committees, employment by the Aboriginal Community Controlled Health Organisations, functioning of community advisory/engagement groups among others including subjective assessments.

### Study participants & eligibility

#### Inclusion/exclusion criteria

##### Cohort study

Routinely collected data will be extracted for all women within the historical and intervention time periods who gave birth (or were booked to give birth) to a First Nations baby in the study sites (2013–2022). Exclusions will be based on standard and/or previously used methods to ensure validity and rigour.

##### Women’s surveys and interviews

Women aged 14 years and over, pregnant with a First Nations baby and booked for maternity care in either research setting are eligible to participate. Of women in the new care models, we estimate approximately 50% will complete the pregnancy survey. From that group, we estimate based on our previous work, a 70% response rate at 2-months postpartum and a 50% response rate at 6-months postpartum. Of the women recruited to participate in surveys, we estimate approximately 10% will be interviewed.

##### Eligibility

Women are eligible to participate if they:Are 14 years and over;Are having a First Nations baby;Obtained their maternity care through *Minga Gudjaga* (rural Birthing on Country service), or through *Binji & Boori*, or obtained standard maternity care; and are planning to birth in the catchment area;Obtained their maternity care through *BiOC North* (urban Birthing on Country service), or obtained standard maternity care; and are planning to birth in the catchment area;Provide consent.

##### Health staff surveys and interviews

Health and support workers providing care for families in either setting will be invited to participate in a staff survey and/or interview or focus group discussion. We anticipate from previous experience most MGP midwives within the Birthing on Country service complete surveys and agree to be interviewed. Some hospital staff may participate. Staff are eligible if they have been involved in the planning and/or provision of care including family support, as part of the maternity journey for First Nations families in catchment areas during the study period.

#### Power and sample sizes

BOOSt has been powered to detect a clinically significant change in preterm birth [53]. Preterm birth rates for First Nations babies in the Illawarra Shoalhaven Local Health District have been reported over a recent 5 year period as between 10.3 and 17.5%, average 12.9%. Based on our observations in the IBUS study [19], we propose a minimum treatment effect of 50% reduction (Odds ratio OR 0.5) for the preterm birth rate in the innovation arm. During recruitment, we will aim to access routinely collected maternity data for approximately 687 women at the rural site and 614 from the urban site (based on an estimated 20% attrition rate). From commencement of the new model of care, we will aim to obtain data from a minimum of 296 births (rural site) and 264 (urban). Given small numbers in the rural site (~ 120 births of First Nations babies attending Birthing on Country per year) and a ~ 3.5 year post-intervention study timeframe, we estimate 70% of the total sample to be in the pre-intervention group and 30% post-intervention. To detect this difference with 80% power and a type 1 error of 5%, and factoring exclusions for ~ 7% twin babies/babies with fetal anomaly, and 10% missing data, 983 women/births in total are needed, which includes 687 in pre-intervention and 296 in post-intervention groups. This sample size will also enable enough power for primary infant and maternal outcomes. For the urban site, the required sample size would be 878: 614 in pre-intervention and 264 in post-intervention groups. For the sub-studies, the sample size will be determined according to qualitative research conventions and considerations around data saturation.

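### The sample-size section states two different design effects (a 50% reduction and OR 0.5) as one and gives two loss figures for the same numbers; at OR 0.5 the planned odds-ratio analysis has about 73–76% power, not 80%

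*Protocol article*

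**What the plan says.** All design figures are in the protocol article, under Power and sample sizes.

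- Baseline: rural preterm birth rates are given "as between 10.3 and 17.5%, average 12.9"%.
- Effect: "we propose a minimum treatment effect of 50% reduction (Odds ratio OR 0.5) for the preterm birth rate in the innovation arm".
- Error rates: "To detect this difference with 80% power and a type 1 error of 5"%. The test, the variance formula and the sidedness are not named.
- Split: "we estimate 70% of the total sample to be in the pre-intervention group and 30% post-intervention".
- Losses: the 687 rural and 614 urban records are first described as "based on an estimated 20% attrition rate". The total is then derived by "factoring exclusions for ~ 7% twin babies/babies with fetal anomaly, and 10% missing data".
- Result for the rural site: "983 women/births in total are needed, which includes 687 in pre-intervention and 296 in post-intervention groups". The 296 is described as a minimum.
- Urban site: 878 (614 + 264), with no urban baseline rate.

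Under Quantitative data, the article plans odds ratios with 95% confidence intervals for binary outcomes and lists logistic regression among the methods.

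**The concern.** A halved risk and a halved odds are close only when the outcome is rare. At 12.9% they differ enough to matter for power, yet the section presents one as the other. Preterm birth is the outcome on which the study is powered, and results will be reported as odds ratios. A reader will therefore compare the estimate with OR 0.5 and assume 80% power for it. If the sample was sized for the larger effect, or for a test other than the planned one, that assumption is wrong. The two loss figures raise the same difficulty: they cannot both be the allowance behind 687.

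**Working it through.** **Inputs** (Power and sample sizes): p1 = 0.129; post/pre ratio k = 30/70 = 0.4286; 80% power; 5% type 1 error. I assume a two-sided test, so (1.960 + 0.842)² = 7.849.

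**The two effects**
- 50% reduction: p2 = 0.129 × 0.5 = 0.0645. OR = (0.0645/0.9355)/(0.129/0.871) = 0.466.
- OR 0.5: odds = 0.5 × 0.129/0.871 = 0.07405, so p2 = 0.07405/1.07405 = 0.0689. RR = 0.0689/0.129 = 0.534, a 46.6% reduction.

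**Reproducing 983**

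Pooled: n1 = [1.960√(p̄(1−p̄)(1+1/k)) + 0.842√(p1(1−p1) + p2(1−p2)/k)]² / (p1−p2)², with p̄ the weighted mean rate.

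Unpooled: n1 = 7.849 × [p1(1−p1) + p2(1−p2)/k] / (p1−p2)².

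In both, n2 = k × n1.

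| Effect | Variance | Evaluable (pre + post) | ÷ 0.83 | ÷ 0.80 | × 1.2 |
|---|---|---|---|---|---|
| RR 0.5 | pooled | 571.2 + 244.8 = 816 | 983 | 1,020 | 979 |
| OR 0.5 | unpooled | 570.5 + 244.5 = 815 | 982 | 1,019 | 978 |
| OR 0.5 | pooled | 670.4 + 287.3 = 958 | 1,154 | 1,197 | 1,149 |
| RR 0.5 | unpooled | 477.6 + 204.7 = 682 | 822 | 853 | 819 |

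The first two rows both land on the stated total to within one birth. The stated inputs therefore do not identify the effect. The 17% allowance (7% + 10%) fits; 20% applied by division gives about 1,020.

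**Power at the stated size.** Evaluable numbers are 687 × 0.83 = 570 and 296 × 0.83 = 246, or 550 and 237 with 20% loss. The values below come from exact binomial enumeration.

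| Test | OR 0.5, 17% loss | OR 0.5, 20% loss | RR 0.5, 17% loss | RR 0.5, 20% loss |
|---|---|---|---|---|
| Log-odds-ratio Wald | 73% | 72% | 80% | 79% |
| Pooled z (chi-square) | 74% | 72% | 81% | 79% |
| Likelihood ratio | 76% | 74% | 83% | 81% |
| Unpooled risk difference | 79% | 78% | 85% | 84% |

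The Wald and likelihood-ratio rows are the tests that belong to a logistic model. Part of the advantage of the unpooled test is a looser error rate: with 570/246 and 12.9% in both groups, it rejects in the direction of benefit 3.2% of the time, against a nominal 2.5%.

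**The case against.** The strongest objection is that the stated total may be a correct calculation for OR 0.5. No variance formula is named, and the unpooled formula at OR 0.5 gives 982, with a pre-intervention group of 687.4 against the stated 687. This stands. A reader might infer that 983 can come only from RR 0.5 and that 80% is therefore a proven arithmetic error. The documents do not support that: by the unpooled formula, nominal power at OR 0.5 is 80%. Even so, that route makes the 50% reduction the wrong label, and it sizes the study on a risk-difference test, whereas the article plans odds ratios.

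A second objection is that 296 is a minimum. About 120 rural births a year over about 3.5 years is 420; less 17% that is about 349, and with 570 pre-intervention births power at OR 0.5 is about 83%. This stands too, and it limits the practical damage. It does not correct the power claimed for 687/296.

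Third, 20% used as a multiplier gives 978–979, close to 983. So the 20% figure could be a rounded description, but the section also spells out 7% and 10% and does not reconcile the two.

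A reader might also infer the same shortfall at the urban site. With no urban baseline rate, that can be shown only by back-solving one from 878, which assumes the answer: about 14.3% under RR 0.5 pooled, about 14.6% under OR 0.5 unpooled.

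**Conclusion.** The point holds as an inconsistency in the stated design. One of the two effects is wrong as written, because at 12.9% they are 6.45% and 6.89% (OR 0.47 against 0.50). The documents do not settle which one produced 983.

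At the minimum 687/296 less 17%, the odds-ratio analysis has about 73–76% power at OR 0.5 and about 80–83% at RR 0.5. The shortfall at OR 0.5 is thus about 4–7 points against the stated 80%. Taking 20% loss instead removes a further 1–2 points. These figures assume a two-sided 5% test, a 12.9% baseline and an unadjusted comparison. No conclusion is drawn about urban power.

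**What to change.** In Power and sample sizes, state one effect, the test and its variance assumption, and take one of two routes:

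- state RR 0.5 (12.9% to 6.45%, OR 0.47) with 80% power; or
- keep OR 0.5 (12.9% to 6.89%) and restate power at the minimum 687/296 as about 73–76% for the odds-ratio analysis. The authors may add that about 420 post-intervention births, if reached, would bring it above 80%.

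The authors should choose according to the calculation they actually ran. Use one loss figure throughout: 17% matches 983; if 20% is meant, restate the power accordingly. For the urban site, give the baseline rate behind 878. Until then, make no urban power statement, or label it an assumption.

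The cost is one or two sentences and, on the second route, a less favourable power figure. No extra births are required.

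### The claim that the sample size is also adequate for the other primary outcomes has no calculation behind it, and if only preterm birth changes, single-site power for Healthy baby is below 80%

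*Protocol article*

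**What the plan says.** Under Power and sample sizes, the protocol article says "BOOSt has been powered to detect a clinically significant change in preterm birth". The rural preterm rate over five years is given as "between 10.3 and 17.5%, average 12.9" per cent, and the target is stated thus: "we propose a minimum treatment effect of 50% reduction (Odds ratio OR 0.5) for the preterm birth rate in the innovation arm". On allocation, "we estimate 70% of the total sample to be in the pre-intervention group and 30% post-intervention". With 80% power, a 5% type 1 error, about 7% exclusions and 10% missing data, the rural total is 983 (687 + 296). Directly after this comes: "This sample size will also enable enough power for primary infant and maternal outcomes". The urban total of 878 (614 + 264) follows, without an urban preterm rate.

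Under Outcome measures there are three primary maternal outcomes (early first visit, number of visits, normal birth) and three primary infant outcomes. One of the infant outcomes is "Healthy baby (live born, singleton, > = 37 weeks gestation, 2500–4499 g birthweight, Apgar score at 5 minutes ≥7"). The power section gives no baseline proportion or target effect for any primary outcome except preterm birth.

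**The concern.** A condensed article may leave secondary power calculations to the full protocol. This sentence, however, is a positive claim about the design, and it can be tested against the inputs printed beside it.

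Healthy baby is the outcome for which the test has most bite, because it contains preterm birth. Halving preterm birth from 12.9% can raise the Healthy baby proportion by at most 6.45 percentage points unless something also changes among term babies. Term babies who are stillborn, outside the weight range or have a low Apgar score fail as well. They add variance and, if their rate is unaffected, no benefit. A sample that only just suffices for preterm birth therefore cannot suffice for Healthy baby under that same effect.

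If the sentence stays as it is, a non-significant Healthy baby result from one site may be taken as coming from an adequately powered comparison, in a study meant to inform scale-up.

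**Working it through.** **Inputs from the document.** Rural baseline 12.9%; 50% reduction; 687 and 296 births; 7% + 10% loss; 80% power; 5% type 1 error. Sidedness is not stated, so two-sided is assumed. Analysed births are 687 × 0.83 = 570 and 296 × 0.83 = 246 (rural), and 614 × 0.83 = 510 and 264 × 0.83 = 219 (urban).

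**Formula.** Power = Φ[(|p1 − p2| − 1.96·s0)/s1]. Here s0 is the standard error with the pooled proportion and s1 the standard error with the separate proportions.

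**Reproducing the plan's figure.** For 12.9% against 6.45% at 70:30, the required net total is 816 to 817. Dividing by 0.83 gives 983 to 984, against the stated 983. At 570 v 246, s0 = 0.02383 and s1 = 0.02103, so (0.0645 − 0.0467)/0.02103 = 0.846 and power is 80.1%. There is no reserve. (An odds ratio of 0.5 gives 6.89% and about 1,154 births, so 983 rests on the halved-rate reading. Under the odds-ratio reading, preterm birth itself has about 73% power.)

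**Healthy baby, effect through preterm birth only.** Let q be term failures per birth at baseline. This figure is not in the document; 2, 5 and 10 per 100 are assumptions. Control failure is 0.129 + q. In the innovation group there are two versions:

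- Constant rate among term births: 0.0645 + (q/0.871) × 0.9355.
- Fixed number per birth: 0.0645 + q.

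Example, q = 0.05 at constant rate: 17.9% against 11.82%, difference 0.0608, s0 = 0.02801, s1 = 0.02611. Then (0.0608 − 0.0549)/0.02611 = 0.226, and power is 59%.

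| Setting | Version | q = 2 | q = 5 | q = 10 per 100 |
|---|---|---|---|---|
| Rural, 570 v 246 | constant rate | 71% | 59% | 45% |
| Rural, 570 v 246 | fixed number | 73% | 65% | 55% |
| Urban, 510 v 219, preterm 14% assumed | constant rate | 70% | 59% | 45% |
| Urban, 510 v 219, preterm 14% assumed | fixed number | 73% | 65% | 56% |

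At only 1 term failure per 100, rural power is already 75% to 76%. The direction does not depend on the assumed q; the size does.

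**What would restore 80%.**

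- A further effect at term. At 570 v 246 the total reduction in failures must be about 6.9, 7.6 or 8.4 points for q = 2, 5 or 10. That is about 0.5 to 2.0 points beyond the 6.45 from preterm birth.
- More births. About 120 a year for about 3.5 years is 420, or 349 after 17% loss. Against 570 this gives 81% to 84% at q = 2, 70% to 76% at q = 5 and 55% to 66% at q = 10.
- Pooling. With 1,080 v 465, 12.9% assumed at both sites and clustering ignored, the constant-rate version gives 94%, 86% and 72%, and the fixed-number version 95%, 91% and 83%.

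**The case against.** The strongest reply is that the answer turns on quantities the document does not state.

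- **Term failures and the urban baseline are not given.** This is correct. The percentages above are illustrations across a stated range and not a property of the protocol. A reader might infer that the protocol's own figures put Healthy baby power at some fixed value below 80%. They do not.
- **The service may help term babies too.** The primary hypothesis is broad improvement in maternal and newborn outcomes. If an odds ratio of 0.5 applied to the whole composite, rural power would be 79%, 86% and 93% at q = 2, 5 and 10. This stands as a possibility, but the protocol quantifies no such effect.
- **The sites may be combined, and 296 is a minimum.** The section on routinely collected data describes comparisons across both sites and multilevel modelling. Both points stand, as the figures above show. However, the power section sizes each site separately, and the sentence follows the rural 983.
- **The remaining primary outcomes show no error.** This is right. At the rural site the detectable differences at 80% power are about 8 to 11 points for baselines between 30% and 80%, which contradicts nothing stated. A reader might infer that these outcomes are underpowered too, but without baselines or target effects that cannot be said.
- **Nothing says null results will be read as no effect.** Odds ratios with 95% confidence intervals are already planned. The risk of misreading comes from the adequacy sentence itself.

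**Conclusion.** The concern holds in a limited form. The sentence asserts a power property that the design is not shown to have. For Healthy baby, the design lacks that property at a single site, at the planned minimum sample, if halved preterm birth is the only effect. The conclusion that power falls below 80% needs only the composite's definition, the protocol's own preterm calculation (80.1%) and a term-failure rate that is not negligible.

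The size of the shortfall is conditional: roughly 45% to 73% at the rural site for assumed term failures of 2 to 10 per 100 births, and similar at the urban site with an assumed preterm baseline of about 14%. It would shrink or disappear with a benefit among term babies, with about 420 post-intervention births and rare term failures, or with pooled sites (about 72% to 95%). The documents do not support saying that adequate power is impossible for Healthy baby, or that it is absent for the other primary outcomes.

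**What to change.** Withdraw or qualify the sentence and restate the power:

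1. Say that the per-site sample is powered for preterm birth only.
2. For each other primary outcome, give the baseline proportion from the historical records and the smallest difference detectable at 80% power with the expected analysed numbers (570 v 246 rural and 510 v 219 urban at the planned minimum). Add the pooled figure if a pooled comparison is the intended analysis.
3. State that Healthy baby has less than 80% single-site power for the effect implied by the preterm target alone, and that a null result will be interpreted from its confidence interval. If a further effect among term babies is expected, state it and show the power under it.

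The cost is a change of wording and a short calculation from records the study will already hold. The stated power becomes less favourable. No more births are needed.
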